**Methods:**

In this randomized, placebo-controlled, single-blinded trial, fifty-six people with PSD will be randomly allocated into the intervention (*n*=28) or control (*n*=28) groups. The intervention group will receive acupuncture treatment, and the control group will receive sham acupuncture treatment, in 20 sessions over 4 weeks. The primary outcome is the change from baseline in the Hamilton Depression Scale-17 (HAMD-17) scores at week 4. Secondary outcomes include the Wisconsin Card Sorting Test (WCST) and latency and amplitude of P1, N170, and P3 of the event-related potentials (ERPs) components to assess the changes in cognitive function and electroencephalography. Outcomes are assessed at baseline and post intervention.

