### Intervention

The enrolled PSD participants receive basic treatment for stroke: basic pharmacotherapy treatment for ischemic stroke and other diseases (such as hypertension, coronary heart disease, and diabetes), and physical therapy and occupational therapy for motor dysfunction will occur every day over 60 min (including preparation). Participants cannot receive antidepressant medication, or on any other acupuncture treatments that may affect the evaluation of the efficacy of the interventions of the study. The participants’ psychological condition will be closely monitored by a psychiatrist throughout the study period. Participants would be withdrawn from the study should any sign of deterioration in mental health condition and will be treated by a psychologist. The acupuncture group will receive acupuncture treatment, and the control group will receive sham acupuncture treatment. The participating physicians in the trial are acupuncture doctors at the Secondary Medical College of Guangzhou University of Traditional Chinese Medicine. As the acupuncturists are responsible for the acupuncture treatment, they are all highly qualified, have a master’s degree in acupuncture and moxibustion, have undergone training in a unified standardized operation plan. Acupuncture treatment will be administered in the supine position, and the temperature of the treatment room is maintained at 26 °C. Participants will receive 20 treatment sessions over a 4-week period at a frequency of 5 times per week.

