### Follow-up

To evaluate the persistence of the effects, a follow-up assessment will occur 1 month after the end of the 4-week treatment.

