### Outcome measures

The endpoints will be evaluated at baseline (before intervention), week 4 (immediately after intervention), and week 8 (1-month follow-up). We include two figures to show the participant timeline more clearly (see Figs. 1 and 2).

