### Sample size

The study uses the HAMD-17 as the primary outcome measure for sample size calculation. The sample size was calculated using the following formula for the comparison of two samples:
$$ n=\frac{{\left({Z}_{1-\frac{a}{2}}+{Z}_{1-\beta}\right)}^2\times \left({\sigma}_1^2+{\sigma}_2^2\right)}{\delta^2} $$

In this study, a two-tailed test was chosen; σ_1_ and σ_1_ represent the difference in the change in HAMD-17 scores after treatment in the test group (acupuncture group) and placebo group (control group), respectively, and δ represents the difference between the two groups. Power Analysis and Sample Size software (PASS; version 11; NCSS Statistical Software, Kaysville, UT, USA) was used for sample size calculation. According to the results of a pilot study [26], σ_1_=9.50, σ_2_=7.42, δ=2.08, *α*=0.05, $$ {Z}_{1-\frac{a}{2}} $$=1.96, *β*=0.1, and *Z*_1 − *β*_=1.28. The calculated sample size of each group was approximately 22 individuals to achieve a power of 0.90 at a significance level of 0.05. After accounting for an anticipated dropout rate of 20%, the total number of patients required for this trial was 56, with 28 in each group.

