#### Data collection methods

Before study initiation, all researchers and acupuncturists will participate in a 2-day training session including assessment and collection of outcome, baseline, and follow-up organized by the Secondary Medical College of Guangzhou University of Traditional Chinese Medicine. During the follow-up period, participants are requested to return to the clinic to receive assessment and will be given subsidies to cover transportation. If the participants could not complete the entire study, and lost to follow-up, these data will be included in the statistics and should be analyzed intentionally.

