### Statistical analysis

Descriptive statistics will be used to describe demographic data of sample groups, while the normality of the distribution of each parameter will be checked by histogram and the Kolmogorov-Smirnov test. The continuous variables will be presented in mean and standard deviation (SD). A chi-squared test will be used to assess sample characteristics and gender. The data that conform to normal distribution will be analyzed by one-way analysis of variance, while the nonconforming data will be analyzed by Mann-Whitney *U* test. The latency and amplitude of the ERP data will be analyzed by mixed-effect model analysis, the Greenhouse-Geisser adjustment will be applied to adjust the degrees of freedom if the assumption of Mauchly’s test of sphericity is not significant. *P* < 0.05 will be taken as the standard for a significant difference. Data analysis will follow the intention-to-treat principle including participants who are randomly assigned. Missing data will be input with the last observation carried forward method.

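### LOCF scores every participant without a week-4 HAMD-17 as exactly zero change on the primary endpoint, which dilutes the effect and biases it if early dropout differs by arm

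*Protocol article*

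**What the plan says.** The abstract of the protocol article defines the endpoint: "The primary outcome is the change from baseline in the Hamilton Depression Scale-17 (HAMD-17) scores at week 4". The Outcome measures section gives the schedule: "The endpoints will be evaluated at baseline (before intervention), week 4 (immediately after intervention), and week 8 (1-month follow-up". The text lists no HAMD-17 assessment between baseline and week 4, and none at early termination.

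The Statistical analysis section sets the analysis population, "Data analysis will follow the intention-to-treat principle including participants who are randomly assigned", and the only missing-data rule in the article, "Missing data will be input with the last observation carried forward method". Data collection methods adds, for participants who do not complete or are lost, that "these data will be included in the statistics and should be analyzed intentionally".

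Three other statements bear on the point:

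- Sample size expects losses ("After accounting for an anticipated dropout rate of 20" per cent) and sets 28 per group.
- Intervention states: "Participants would be withdrawn from the study should any sign of deterioration in mental health condition".
- Follow-up gives the purpose of the week-8 visit: "To evaluate the persistence of the effects, a follow-up assessment will occur 1 month after the end of the 4-week treatment".

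**The concern.** With one assessment before the endpoint, last observation carried forward is baseline carried forward. The imputed change is baseline minus baseline, which is zero, and it is analysed as if it had been measured. If participants improve on average, as the planning figures suggest, zero is the wrong value for a typical missing participant.

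Nor is zero reliably cautious. A participant withdrawn because mental health is deteriorating is scored as unchanged, which is better than the true state. That withdrawal rule also means that missingness can depend on outcome.

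The primary estimate therefore mixes the treatment effect with the proportion lacking a week-4 score in each arm. At stake are the size of the estimate, the power of a small trial and, if early loss differs by arm, the validity of the test.

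A lesser point concerns week 8. There LOCF copies the week-4 score forward for anyone missing, and so assumes the persistence that the visit is meant to evaluate. The primary and secondary outcomes are set at week 4, so this is secondary.

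**Working it through.** **Inputs from the Sample size section.** 28 per group (22 before dropout), 20% dropout, two-sided α 0.05, power 0.90, δ = 2.08, and 9.50 and 7.42 printed as σ₁ and σ₂.

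**The plan's own figure.** Its formula gives (1.96 + 1.28)² × (9.50² + 7.42²) / 2.08² = 352.6, so 353 per group rather than 22. The dropout step does reproduce: 22 / 0.8 = 27.5, rounded up to 28. Since 9.50 − 7.42 = 2.08 = δ exactly, the two values look like mean changes, and they are read that way here. That the stated 22 does not follow from the formula is a separate matter.

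**SD range.** Solving the formula for a common SD at n = 22 gives √(22 × 2.08² / (2 × 3.24²)) = 2.13. Reading the printed values as SDs gives √((9.50² + 7.42²) / 2) = 8.52. Results are shown from 2.13 to 8.52.

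**Estimate under LOCF.** With k of 28 missing at week 4, unrelated to outcome within arm, the expected arm mean is (28 − k)/28 × mean change. 20% of 28 is 5.6, about 6.

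- 6 and 6 missing: (9.50 − 7.42) × 22/28 = 1.63.
- 3 acupuncture, 9 sham: 9.50 × 25/28 − 7.42 × 19/28 = 3.45.
- 9 acupuncture, 3 sham: 9.50 × 19/28 − 7.42 × 25/28 = −0.18.
- No true effect (both means (9.50 + 7.42)/2 = 8.46), 3 versus 9: 8.46 × 6/28 = 1.81.
- No true effect, 4 versus 8: 8.46 × 4/28 = 1.21.
- Each excess dropout in one arm: 8.46/28 = 0.30 points.

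For mean changes of 5 to 10, the 3-versus-9 false difference is 5 × 6/28 = 1.07 to 10 × 6/28 = 2.14, and the shift per excess dropout is 0.18 to 0.36.

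**Power.** Simulated trials, normal changes, two-sided t-test (identical to one-way ANOVA for two groups), 20,000 runs. At SD 2.13:

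- 28 per arm, no dropout: 95%.
- 22 completers per arm, nothing imputed: 89%.
- LOCF, exactly 6 missing per arm: 15%.
- LOCF, each participant missing with probability 6/28: about 33%.

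The loss comes from the block of zeros as well as from the smaller estimate. With random dropout the variance is (1 − p)·SD² + p(1 − p)·mean² with p = 6/28, so the arm SDs rise from 2.13 to 4.33 and 3.58. If the zeros led the normality check to the Mann-Whitney test, power with exactly 6 per arm would be 53% (2,000 runs). At SD 8.52 the t-test goes from about 15% without dropout to 8% with exactly 6 per arm.

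**Rejection rate with no true effect (t-test):**

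| Missing, acupuncture v sham | False difference | Fixed counts, SD 2.13 / 4 / 6 / 8.52 | Random with those probabilities, same SDs |
|---|---|---|---|
| 6 v 6 | 0 | at most about 3% | about 5% throughout |
| 4 v 8 | 1.21 | 4 / 7 / 7 / 6–7% | 21 / 15 / 11 / 9% |
| 3 v 9 | 1.81 | 30 / 21 / 15 / 11% | 41 / 28 / 19 / 13% |

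Analysing completers only in the same scenarios, without inserted zeros, keeps the rate at about 5%.

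**The case against.** Several objections have force.

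*Not every dropout is affected.* This stands. Someone lost between week 4 and week 8 has a real week-4 score. The 20% carries no time point, and some of it may fall in follow-up, so placing all of it before week 4 is an assumption.

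*A reader might infer that LOCF makes a false positive likely, or that dropout counts rather than treatment will decide the result.* The documents do not support that. They give no expected difference in dropout between arms: the antidepressant ban applies to both, participants are blinded, and the Control group section argues that the sham is credible. If dropout is unrelated to arm, the rejection rate stays near 5%. With 12 dropouts in all, chance alone gives a split of 3–9 or worse about 10% of the time. Fixed 4 versus 8 gives only 4–7%. The inflation needs dropout that truly differs by arm. The outcome-dependent withdrawal rule makes that possible but does not establish it.

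*The sizes rest on a reinterpretation.* This also stands. If 9.50 and 7.42 really are SDs, power is about 15% before any dropout, and the sample size is then the larger problem.

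*An unseen analysis plan or figure may deal with this.* Missing sensitivity analyses alone would be no finding. But LOCF is stated, not left open. Figures 1 and 2 are not available, so an interim HAMD-17 shown only there cannot be excluded; the written schedule lists none.

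None of this removes the dilution and power loss under balanced early dropout, or the bias under unequal early dropout.

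**Conclusion.** The point holds in this form: LOCF on the stated schedule assigns zero change on the primary endpoint to every participant without a week-4 HAMD-17, and treats that value as data. The mechanism follows from the schedule, the analysis population and the imputation rule, and needs none of the planning numbers. That zero is the wrong value requires only that participants change on average.

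Under balanced early loss the harm is a smaller estimate and lost power, not a false positive. Under loss that differs by arm the estimate shifts in proportion to the excess, by about 15% of the planned effect per excess dropout (0.30/2.08), and it can be inflated, erased or slightly reversed. Because deteriorating participants would be scored as unchanged, the rule cannot be defended as conservative.

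Confidence in the mechanism is high. Confidence in the exact sizes is limited: they assume that the printed sigmas are mean changes, that the 20% dropout falls before week 4, that missingness is unrelated to outcome within arm, and an SD between 2.13 and 8.52.

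**What to change.** In the Statistical analysis section, replace LOCF for HAMD-17 with one of the following:

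- a likelihood-based repeated-measures model of HAMD-17 at baseline, week 4 and week 8, with baseline in the outcome vector and constrained equal between arms, and the week-4 contrast as primary. Participants with baseline only then stay in the analysis without an invented week-4 value, and week 8 no longer rests on copied scores; or
- multiple imputation of the missing scores using baseline and arm.

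Add one sensitivity analysis, either a delta shift or imputation referenced to the sham arm, because withdrawal can depend on outcome. Record the change before unblinding for analysis.

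The cost is revised wording and slightly more analysis work, with no new data. The team already plans mixed-effect models for the ERP outcomes. The downside is that the primary analysis then relies on a missing-at-random assumption, which the sensitivity analysis is there to test. Neither method recovers the information lost with missing scores; the gain is that false zeros are not added to that loss.

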### Ethics and dissemination

This study was approved by the ethics committee of the Secondary Medical College of Guangzhou University of Traditional Chinese Medicine, China, on 6 September 2019 (approval No. ZF2019-170-01). Protocol revision, adverse reaction reports, and annual review will be supervised by the ethics committee of the Secondary Medical College of Guangzhou University of Traditional Chinese Medicine. The research observers will explain the study to participants before they voluntarily sign the informed consent form at the beginning of the study. Participation in the study is voluntary and can be discontinued at any time. The decision not to participate will not affect the patient’s care. On the consent form, participants will be asked to grant permission for the research team to share relevant data with the researchers taking part in the research or regulatory authorities, where relevant. Participants will also be asked if they agree to the use of their data, should they choose to withdraw from the trial. This trial does not involve the collection of biological specimens for storage. Information provided by participants will only be shared with members of the research team. We will make every effort to keep the participants’ information confidential. All paper documents related to the study will be kept in a locked cabinet. All participants’ information will be kept strictly confidential. Clinical examination and acupuncture treatment related to this study are provided free of charge during the study period. All participants will be reimbursed for travel expenses to encourage adherence during the follow-up phase.

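### Carrying the week-4 score forward to a missed week-8 visit assumes the persistence that the visit is meant to measure; the effect is small and a single repeated-measures model removes it

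*Protocol article*

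**What the plan says.** All references are to the protocol article.

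- **Follow-up** gives the later visit one purpose: "To evaluate the persistence of the effects, a follow-up assessment will occur 1 month after the end of the 4-week treatment".
- **Outcome measures** schedules the endpoints at baseline, week 4 and week 8 only, so week 4 is the last value available before week 8.
- **Statistical analysis** sets one rule for gaps: "Missing data will be input with the last observation carried forward method". It names no exception for week 8 and no alternative or sensitivity analysis. The same section analyses everyone randomised, and Data collection methods keeps those lost to follow-up in the analysis.
- **Intervention** says that each participant's "psychological condition will be closely monitored by a psychiatrist throughout the study period", and that "Participants would be withdrawn from the study should any sign of deterioration in mental health condition".
- **Ethics and dissemination** states: "All participants will be reimbursed for travel expenses to encourage adherence during the follow-up phase".
- **Sample size** allows for 20% dropout without saying when it occurs. **Primary outcome** and **Secondary outcomes** are set at week 4.

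**The concern.** Carry-forward enters a change of exactly zero between weeks 4 and 8 for anyone who attends the first visit and misses the second. Week 8 is there to find out whether that change is zero. For these participants the imputation supplies the answer.

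At stake is the statement the trial will make about durability. If the benefit fades after treatment stops, copied week-4 scores make it look more lasting than it is when week 8 is set against week 4. Withdrawal for deterioration may add to this. If that rule operates after week 4, as its wording suggests, a participant withdrawn because of relapse would keep the better week-4 score.

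**Working it through.** **Inputs from the protocol article.** Planned difference 2.08 HAMD-17 points, 20% dropout and 28 per arm (Sample size); visits at baseline, week 4 and week 8 (Outcome measures); carry-forward throughout (Statistical analysis). The dropout step reproduces: 22/(1 − 0.20) = 27.5, rounded up to 28 per arm. The value 2.08 serves here only as a scale; whether 22 per arm follows from the stated inputs is a separate matter.

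**Assumed, because the document does not give them.** f1 is the share lost before week 4, f2 the share lost between weeks 4 and 8, and r the true fraction of the week-4 effect still present at week 8. Loss is taken as equal in both arms and unrelated to the size of the effect.

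**Step 1: what carry-forward reports.** Those lost before week 4 carry baseline forward and contribute no change at either visit. Those lost later carry week 4 forward.

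- Week-4 difference = (1 − f1) × 2.08
- Week-8 difference = [(1 − f1 − f2) × r + f2] × 2.08

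**Step 2: week 8 relative to week 4.** Dividing the second by the first gives

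apparent retained fraction = r + f2(1 − r)/(1 − f1).

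**Step 3: the week-8 difference itself.** Subtracting the true value r × 2.08 gives

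bias = 2.08 × [f2(1 − r) − f1 × r] points.

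| Loss before / after week 4 | Apparent retention, r = 0 | Apparent retention, r = 0.5 | Bias at week 8, r = 0 | r = 0.5 | r = 1 |
|---|---|---|---|---|---|
| 15% / 5% | 0.104/1.768 = 6% | 0.936/1.768 = 53% | +0.10 | −0.10 | −0.31 |
| 10% / 10% | 0.208/1.872 = 11% | 1.040/1.872 = 56% | +0.21 | 0 | −0.21 |
| 5% / 15% | 0.312/1.976 = 16% | 1.144/1.976 = 58% | +0.31 | +0.10 | −0.10 |
| 0% / 20% (bound) | 0.416/2.08 = 20% | 1.248/2.08 = 60% | +0.42 | +0.21 | 0 |
| 20% / 0% | 0% | 50% | 0 | −0.21 | −0.42 |

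The retained fraction is never too low in this table. It is correct when nobody is lost after week 4, or when r = 1. The difference in points changes sign, because baseline carried forward for early losses shrinks it while week 4 carried forward for late losses props it up.

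**Step 4: unequal loss.** As an illustration, read the 9.50 and 7.42 in Sample size as mean changes. This is an assumption: the text labels them as σ, although 9.50 − 7.42 = 2.08. With r = 0 and losses only after week 4:

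- 30% lost on acupuncture and 10% on sham: 9.50 × 0.30 − 7.42 × 0.10 = +2.11 points
- the reverse: 9.50 × 0.10 − 7.42 × 0.30 = −1.28 points

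**Step 5: against sampling error.** A simulation with 28 per arm and a 10/10 split (assumed SD 5, correlation 0.6, week-8 loss depending on the week-4 score) gave, at r = 0, a week-8 difference of 0.23 by carry-forward and 0.03 by a likelihood model. The spreads were 1.17 and 1.33, and the root mean squared errors 1.19 and 1.33. Retention came out at 0.12 against 0.01 for r = 0, 0.56 against 0.51 for r = 0.5, and 1.00 by both for r = 1. If 9.50 and 7.42 are SDs, as labelled, the spread without loss is √[(9.50² + 7.42²)/28] ≈ 2.3.

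**Step 6: would replacing week 8 alone be enough?** No. Week 4 would still be shrunk by (1 − f1), and the ratio would become r/(1 − f1). At r = 0.5 this is 0.5/0.90 = 0.556 for the 10/10 split, the same as carry-forward, and 0.5/0.85 = 0.588 for 15/5, worse than carry-forward's 0.529. Both visits must come from the same model.

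**The case against.** The strongest reply has four parts.

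- **No decision rests on week 8.** The primary and secondary outcomes are fixed at week 4, the abstract lists assessments only at baseline and after the intervention, and no week-8 hypothesis or retained fraction is defined. This stands, and it is why the point is minor. It does not remove the point, since Follow-up names persistence as the reason for the visit and the carry-forward rule is stated without exception. A stated rule is not a detail left to an analysis plan.
- **The effect is small.** This also stands. At the 10/10 split the bias is at most 0.21 points against a simulated spread above 1, and carry-forward had the smaller root mean squared error in that simulation. The complaint is that a confidence interval shows sampling error but not an assumption built into the scores.
- **The direction is not fixed.** A reader might infer that carry-forward always overstates the week-8 benefit, or always favours acupuncture. The document does not support that. The sham arm's scores are frozen too, the bias in the difference changes sign with r and with the timing of loss, and unequal loss can push it either way. Only the comparison of week 8 with week 4 moves one way, and only under equal loss.
- **The supporting signs are weak.** Travel payments are a guard against missed visits, not evidence of how many there will be. Relapse hidden by withdrawal after week 4 is plausible but not shown. Both are context here; the finding rests on the imputation rule and the visit schedule.

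**Conclusion.** The point holds in a limited form, at minor severity. As written, the rule scores every participant seen at week 4 but missing at week 8 as having kept the week-4 result exactly, in the month where persistence is to be judged.

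Under equal loss, a vanished effect would appear 6% to 16% retained for splits of the 20% dropout from 15/5 to 5/15, with 20% (0.42 points) as the bound if all loss falls after week 4. The week-8 difference is biased by 2.08 × [f2(1 − r) − f1 × r] points, of either sign and small beside sampling error. These sizes rest on assumed timing of dropout, assumed retention and the plan's difference of 2.08.

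A reader might also infer that the primary outcome is compromised by this argument. It is not: the argument concerns conclusions about persistence, and the definition of the week-4 outcome is unaffected.

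**What to change.** In Statistical analysis, replace carry-forward for HAMD-17 with wording such as:

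*HAMD-17 will be analysed by one likelihood-based repeated-measures model using baseline, week 4 and week 8, with group, visit and group-by-visit terms, assuming data are missing at random. The week-4 and week-8 between-group differences, and their contrast as the measure of persistence, will all be taken from this model. One sensitivity analysis will set the week-8 score of participants withdrawn for deterioration to their baseline score.*

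The sensitivity analysis is needed because the main model would not by itself reveal unrecorded worsening that led to withdrawal.

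**Cost.** One model and one sensitivity analysis on data already scheduled, with no new visits. The team already plans this kind of method: "The latency and amplitude of the ERP data will be analyzed by mixed-effect model analysis". The change also alters how the week-4 difference is estimated, so it should be fixed before unblinding. The downsides are an explicit missing-at-random assumption and a somewhat wider interval (simulated spread about 1.33 against 1.17 at an assumed SD of 5). The gain is that persistence is estimated and no longer assumed; precision does not improve.
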